### Primary outcome measure

The primary outcome measure will be hospital length of stay, calculated from arrival in the emergency department until discharge from the health service, based on date and time (note that data will be collected in minutes but converted to days). This information is routinely collected at the institution for all inpatients.

### Secondary trial outcome measures

Secondary outcome measures comprise routinely collected institutional data and include:Inpatient mortality30 day and 90 day readmission rates and mortalityAdmission to the intensive care unit from inpatient wards and requirement for and duration of mechanical ventilationTotal individual per-separation hospital clinical costing, as determined by the institutional dedicated clinical costing unit using the Power Performance Manager™ software platform (Power Health Solutions, Adelaide, Australia)Protocol adherence (proportion of evidence-based treatments delivered in each group; proportion of patients receiving the whole bundle; reasons for protocol adherence failure)Serious adverse events (including the incidence of in-hospital hyperglycaemia requiring new insulin prescription, adverse drug reactions where it is required that the drug use is stopped, falls or clinical deterioration requiring urgent medical review during early mobilisation), other adverse events and clinical complications (Table 2) occurring prior to admission, during inpatient stay or requiring re-presentation to hospital within 30 days.

**Table 2 Tab2:** Reporting of serious adverse events, adverse events and complications

Complication group	Complication
Pneumonia-associated complications	Respiratory failure requiring intubation
	Hypotension requiring vasopressors
	Empyema *Defined as: documented in registrar admission assessment, radiologist chest X-ray report or medical discharge summary*
	Acute respiratory distress syndrome *Defined as: documented in registrar admission assessment, radiologist chest X-ray report or medical discharge summary*
	Pleural effusion *Defined as: diagnosed on radiologist chest X-ray report*
	Increased confusion from baseline
Other adverse events	Death from any cause
	Fall with fracture
	Cardiac decompensation *Defined as: documented in registrar admission assessment, radiologist chest X-ray report or medical discharge summary*
	Cardiac event *Defined as: diagnosed episode of cardiac ischaemia or new cardiac arrhythmia*
	Acute stroke *Defined as: documented in registrar admission assessment, radiologist report or medical discharge summary*
	Thromboembolic event *Defined as: pulmonary embolus or deep vein thrombosis documented in registrar admission assessment, radiologist report or medical discharge summary*
	Confirmed or suspected gastrointestinal bleeding
Adverse events in patients receiving corticosteroids	Adverse drug reaction where it is required that the drug is stopped (percentage of total number receiving burst corticosteroid dose)
	In-hospital hyperglycaemia requiring new insulin prescription (percentage of known diabetics)
Adverse events compatible with antibiotic use	Adverse drug reaction, where it is required that the drug use is stopped
Adverse events in patients receiving early mobilisation	Falls during physiotherapy (percentage of total physiotherapy sessions delivered)
	Clinical deterioration during physiotherapy requiring urgent medical review (percentage of total physiotherapy sessions delivered) (see Additional file 2)
	Mobilisation ceased owing to sustained observations outside target range (percentage of total physiotherapy sessions delivered) (see Additional file 2)

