### Ascertainment, enrolment and waiver of consent

Ascertainment will be conducted prospectively to identify eligible participants in real time ensuring employment of identical methods of ascertainment for both control and intervention groups. A community-acquired pneumonia service team member will attend each general internal medicine morning clinical handover meeting to identify new admissions with possible respiratory infection from the previous 24 hours. Either the chief medical registrar or treating medical registrar will subsequently review the medical record and chest X-ray (for evidence of a new infiltrate, as per requirements of the standardised case definition) of potential participants to assess eligibility. Those meeting this case definition [34] and eligibility criteria will be enrolled. In situations where the chest radiograph or community-acquired pneumonia diagnosis are not definitive, the treating medical consultant will determine eligibility.

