### Data collection (see Fig. 4)

#### At enrolment (baseline measures)

Demographic and clinical characteristics will be recorded by collection of the following variables (directly from the patient or the medical record): site, patient age and sex, admitting medical unit, eligibility criteria (age, chest X-ray findings, cough, dyspnoea, temperature, chest auscultation findings, peripheral blood leucocyte count), vital signs on admission (temperature, heart rate, blood pressure, respiratory rate, pulse rate, confusion), estimated glomerular filtration rate, residential care status (independent living, supported accommodation, aged care facility), pre-morbid mobility, function and exercise tolerance, CORB score (derived from confusion, oxygenation, respiratory rate and blood pressure), any relevant comorbidities (e.g. diabetes, immunosuppression, adrenal insufficiency, chronic obstructive pulmonary disease, chronic cardiac failure, malignant process), number of routine medications used by the patient, baseline corticosteroid dose (if any), baseline insulin usage, relevant drug allergies, enrolment in a concurrent inpatient research trial, any decision to initiate palliative care on admission, any adverse events or complications that occur prior to enrolment.

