#### Daily during admission (clinical monitoring)

Circumstances necessitating withdrawal of a participant from the study after enrolment but within 48 hours of admission to a general internal medicine unit will be recorded.

The following variables will be collected from the medical record and reported for all enrolled patients: any serious adverse events, adverse events or clinical complications (see Table 2), any decision to palliate, adherence to protocol for Interventions 1 to 4 (as listed previously).

Daily vital signs (SpO_2_, supplementary oxygen requirements, heart rate, respiratory rate, blood pressure, temperature) will be measured every 4 hours as per routine clinical care and used to ascertain the switch to oral from intravenous antibiotics.

Blood glucose readings as clinically indicated and requested by treating team, and oral intake status (ability to tolerate oral medications and absence of gastrointestinal problems that may affect drug absorption) will also be reviewed daily.

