#### At 30 and 90 days following presentation to the emergency department (outcome measures)

Mortality, institutional readmission within 30 and 90 days and total institutional costs incurred at 30 and 90 days will also be extracted from the institutional data warehouse and linked to the study dataset as described previously.

Any adverse event or complication (as defined in Table 2) that requires re-presentation to hospital noted in the electronic medical record within 30 days of initial arrival in the emergency department will be recorded.

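### Complications present before admission are counted in a secondary outcome, so for items that can exist on arrival the comparison includes events the service cannot affect

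*Protocol article*

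**What the plan says.** The list under Secondary trial outcome measures opens with "Secondary outcome measures comprise routinely collected institutional data and include". Its last item covers serious adverse events, other adverse events and the Table 2 complications, "occurring prior to admission, during inpatient stay or requiring re-presentation to hospital within 30 days". That is three time windows in one outcome item.

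In Table 2, empyema, acute respiratory distress syndrome and cardiac decompensation are each defined as "documented in registrar admission assessment, radiologist chest X-ray report or medical discharge summary". Acute stroke and thromboembolic event have near-identical definitions that also accept the admission assessment. Pleural effusion needs only the radiologist's chest X-ray report. Increased confusion, cardiac event and gastrointestinal bleeding carry no onset rule.

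The data collection sections treat the three windows separately:
- At enrolment (baseline measures): "any adverse events or complications that occur prior to enrolment".
- Daily during admission: "any serious adverse events, adverse events or clinical complications (see Table 2".
- At 30 and 90 days: "Any adverse event or complication (as defined in Table 2) that requires re-presentation to hospital", noted within 30 days of first arrival in the emergency department.

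Under Ascertainment, enrolment and waiver of consent, a team member attends morning handover to "identify new admissions with possible respiratory infection from the previous 24 hours". The service therefore meets patients who have already been admitted.

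**The concern.** An outcome used to compare two conditions should be able to respond to the condition. An event that happened before admission cannot respond to a service that finds its patients after admission. Counting such events has two consequences for the affected items.

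- **Dilution.** A similar background of prevalent events is added to both conditions. A true excess or reduction in new complications then looks smaller than it is. For harms, a bias towards no difference is the unfavourable direction.
- **False signals.** If patients in intervention periods happen to arrive sicker or less sick, that difference shows up as a difference in complications even when the service does nothing. There are only eight clusters.

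The same event also plays two roles, as a baseline characteristic in one section and as part of an outcome in another.

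**Working it through.** The article states no adverse-event rate and no power for safety, so there is no figure to reproduce. The check has two parts.

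**1. Which items are affected**

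| Table 2 item | Can it be met by a condition present on arrival? |
|---|---|
| Empyema, acute respiratory distress syndrome, cardiac decompensation, stroke, thromboembolism | Yes; the admission assessment is an accepted source |
| Pleural effusion | Yes; the admission chest X-ray report is recorded (At discharge section), and a new infiltrate on chest X-ray is needed for eligibility, so an effusion on that film qualifies |
| Increased confusion | Yes; there is no onset rule, and confusion is also a baseline variable and a CORB component |
| Cardiac event, gastrointestinal bleeding | Yes; there is no onset rule |
| "In-hospital hyperglycaemia requiring new insulin prescription (percentage of known diabetics" | No; in-hospital by its wording |
| Falls, deterioration or cessation during physiotherapy | No; tied to sessions delivered in hospital |
| Death | No |

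**2. How much it could matter (all rates assumed)**

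For a single item, let p be the proportion with it on arrival, the same in both conditions. Let a and b be the risks of a new event in control and intervention among those without it on arrival. Each patient counts once, so:

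counted risk = p + (1 − p) × new risk

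counted ratio = [p + (1 − p)b] / [p + (1 − p)a]

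counted difference = (1 − p)(b − a)

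True benefit, a = 10%, b = 6%, ratio 0.60:

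| p | Control | Intervention | Ratio | Difference (points) |
|---|---|---|---|---|
| 0 | 10.0% | 6.0% | 0.60 | −4.0 |
| 5% | 0.05 + 0.95 × 0.10 = 14.5% | 0.05 + 0.95 × 0.06 = 10.7% | 0.74 | −3.8 |
| 15% | 0.15 + 0.85 × 0.10 = 23.5% | 0.15 + 0.85 × 0.06 = 20.1% | 0.86 | −3.4 |
| 30% | 0.30 + 0.70 × 0.10 = 37.0% | 0.30 + 0.70 × 0.06 = 34.2% | 0.92 | −2.8 |

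True harm, a = 10%, b = 20%, ratio 2.00. Power is for a two-proportion test at two-sided 5% with n = 320 per condition (half of the 640 under Sample size). With counted risks c and d and their mean m, power = Φ{(|d − c| − 1.96√[2m(1 − m)/n]) / √[(c(1 − c) + d(1 − d))/n]}. This ignores clustering and period effects, so only the fall is informative, not the level.

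| p | Control | Intervention | Ratio | Power |
|---|---|---|---|---|
| 0 | 10.0% | 20.0% | 2.00 | 94.5% |
| 5% | 14.5% | 24.0% | 1.66 | 86% |
| 10% | 19.0% | 28.0% | 1.47 | 77% |
| 20% | 28.0% | 36.0% | 1.29 | 58% |
| 30% | 37.0% | 44.0% | 1.19 | 44% |

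No true effect, new risk 10% in both, but 10% of control and 15% of intervention patients with the item on arrival: 0.10 + 0.90 × 0.10 = 19.0% v 0.15 + 0.85 × 0.10 = 23.5%, ratio 1.24. With the imbalance reversed, the ratio is 0.81.

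**The case against.** The best defence is that the outcome item only summarises what is captured. Table 2 is presented as a reporting table, lists items one by one and gives several their own denominators. The three windows match three separate collection points, so the data should largely allow them to be split. The Statistical methods section promises a detailed plan for secondary analyses, which is not shown. The admission assessment might also have been listed as a source because a patient who re-presents within 30 days has a new one.

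Much of this stands and limits the point. A reader might infer that a pooled any-event rate is diluted, or that the whole safety comparison is compromised. The article supports neither reading. It defines no such composite, and among the serious adverse events it names, in-hospital hyperglycaemia and mobilisation events are untouched. A reader might also infer that seasonal differences in severity pass straight into the result. The model adjusts for period and season as well as age and sex, so what remains is chiefly chance imbalance in severity or complications at presentation, for which no adjustment is stated. The admission assessment as a source does not, on its own, prove that conditions present on arrival were meant to count.

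What does not stand is the idea that nothing needs changing. The pre-admission window is written into the outcome list itself, and no section says that those events are reported apart or used only as baseline. This is a stated rule, not a detail left to a later plan. If separate tabulation was intended, the same correction would say so.

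**Conclusion.** The point holds for the Table 2 items that can be present on arrival, and only for those. As written, their comparison includes events that the service cannot affect, and the outcome section conflicts with the baseline section over what those events are.

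The size cannot be known from the article. In the assumed single-item example, a true ratio of 0.60 reads as 0.74 to 0.92 for arrival prevalences of 5% to 30%. A 5-point chance imbalance on arrival gives 1.24 or 0.81 with no effect at all. These figures assume the stated rates, one count per patient and, for the dilution figures, equal prevalence in both conditions.

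The primary outcome and the sample size are not touched. The correction is worth making because it is nearly free and removes a bias towards no difference.

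**What to change.** 1. In Secondary trial outcome measures, delete the pre-admission window from the adverse-event and complication outcome.
2. Count only events with onset after one anchor that is the same in both conditions, namely admission to the general internal medicine unit, or events at re-presentation within 30 days. Enrolment is a different, later time point and should not be mixed with it.
3. Apply that onset rule to the Table 2 definitions, so that a finding in the index admission assessment or on the admission film does not by itself count.
4. Align the baseline item to the same anchor and use earlier events as baseline description only.

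The cost is wording and a present-on-arrival flag at record review, with somewhat fewer counted events. The data collection sections already gather the windows at separate points, so little new work is needed.

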#### Intervention 1 – Corticosteroids

Treating clinicians will be advised to prescribe 50 mg prednisolone daily for 7 days. See Additional file 2 for details of specific contraindications for corticosteroid therapy.

Patients with diagnosed diabetes will be routinely monitored for hyperglycaemia (see Data monitoring section) and managed at the discretion of the treating team in accordance with existing institutional procedures and practices. All admitted patients have blood glucose levels measured in the emergency department, and ongoing random blood glucose monitoring may also be implemented for other patients thought to be at risk of hyperglycaemia at the discretion of the treating team. Any variation to the dose and duration, such as use of tapered dosage, and time from admission until first dose will also be recorded. Alternative medical reasons given for non-prescription of corticosteroids, or reduced duration of administration, will be noted.

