### Blinding

Clinicians providing patient interventions cannot be blinded, although participants are effectively blinded, owing to the waiver of consent. All primary and secondary outcome measures are routinely collected within the organisation by staff not involved in delivery of the intervention, who will be unaware of participant group allocation. There is therefore little or no potential risk of bias in outcome assessments. A statistician blinded to the allocation sequence will perform data analysis.

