### Data monitoring

Adverse events and adverse drug reactions that are considered to be associated with the delivery of the community-acquired pneumonia service protocolised interventions will be reported to the principal investigator within 72 hours. Patients receiving routine corticosteroids as a component of the community-acquired pneumonia service interventions will be reviewed daily and records will be kept of any hyperglycaemia requiring new insulin treatment. A log of adverse events and adverse drug reactions will be kept and reported to the project steering committee at quarterly meetings, and to the Melbourne Health Human Research Ethics Committee at 3 month intervals.

Serious adverse events and suspected unexpected serious adverse reactions will be reported to the Melbourne Health Human Research Ethics Committee within 72 hours. These may include (but are not limited to):Unexpected deathSerious drug-related adverse event (directly linked to either antibiotic or corticosteroid dose) where it is required that the drug is stoppedA fall with associated patient or clinician injury during physiotherapyPatient deteriorating clinically within 60 min of a physiotherapy session requiring a medical emergency team call or code blue (as defined by institutional procedures)

The project steering committee will meet quarterly to report enrolment numbers, protocol adherence or violations and adverse events and report these to the human research ethics committee. A data monitoring committee was not deemed necessary because outcome measures (e.g. length of stay) are (1) objective, (2) unambiguous and (3) collected through existing routine, validated measures (and therefore not prone to data integrity issues).

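### Four Table 2 harm rates are divided by an exposure that the service is meant to raise, and new-insulin hyperglycaemia is put over known diabetics only

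*Protocol article*

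**What the plan says.** Serious adverse events are a secondary outcome, and the list under Secondary trial outcome measures includes "the incidence of in-hospital hyperglycaemia requiring new insulin prescription", with no denominator. Table 2, in the same section, then sets denominators for five of its 19 rows:

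- Under the group heading "Adverse events in patients receiving corticosteroids", drug reactions that require stopping the drug are a "percentage of total number receiving burst corticosteroid dose".
- Under the same heading: "In-hospital hyperglycaemia requiring new insulin prescription (percentage of known diabetics".
- Under early mobilisation: "Falls during physiotherapy (percentage of total physiotherapy sessions delivered". Clinical deterioration and ceased mobilisation have the same denominator.

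The Control group section gives 2015 audit figures of 43% of patients receiving corticosteroids and 63% receiving physiotherapy. Table 1, item 11, aims for more than 70% and more than 85% under the service. Intervention 3 provides mobilisation daily.

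Statistical methods says that primary and secondary analyses follow the randomised allocation, in a mixed model with unit and period effects. The section on daily data collection says that adverse events are taken from the medical record and reported for all enrolled patients.

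**The concern.** The intervention under test is the service as a whole. The safety question is therefore whether more patients come to harm under the service than under usual care. One route to extra harm is simply that more patients are given steroids and more physiotherapy sessions take place. A rate per recipient or per session divides that route out. It answers a different question: whether each course or session has become riskier.

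The recipients and the sessions are also determined after allocation, by the treatment actually given. Session counts depend in addition on length of stay, which is the primary outcome. A comparison on these bases is not a comparison as randomised.

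The insulin row raises a separate problem. Intervention 1 accepts that patients without diagnosed diabetes can be at risk: "ongoing random blood glucose monitoring may also be implemented for other patients thought to be at risk of hyperglycaemia". A denominator of known diabetics has no place for an event in such a patient.

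The abstract names new-insulin hyperglycaemia and falls during mobilisation as its serious adverse events, and both are among the five rows. Consent is waived and there is no data monitoring committee, so the reported rates carry much of the weight of the safety assessment.

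**Working it through.** The plan states no figure for these harms, so there is nothing to reproduce. The check is on what each denominator can show.

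**Inputs from the article.** Steroid exposure s₀ = 0.43 (audit) and s₁ = 0.70 (lower edge of the target). Physiotherapy exposure s₀ = 0.63 and s₁ = 0.85. Event risks, sessions per patient and diabetes prevalence are not given, so the values below are assumptions.

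**Four exposure-based rows.** Let r be the risk per exposure, equal in both conditions.

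- Rate on the Table 2 basis: r in each condition, ratio r/r = 1.00.
- Rate per enrolled patient: s·r, ratio s₁/s₀.

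Steroid drug reaction: 0.70/0.43 = 1.63, whatever the value of r.

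| Assumed risk per recipient | Usual care, per enrolled patient | Service, per enrolled patient |
|---|---|---|
| 2% | 0.43 × 2% = 0.9% | 0.70 × 2% = 1.4% |
| 5% | 0.43 × 5% = 2.2% | 0.70 × 5% = 3.5% |
| 10% | 0.43 × 10% = 4.3% | 0.70 × 10% = 7.0% |

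On the Table 2 basis each line would show the same percentage in both conditions.

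Physiotherapy harms, with k sessions per treated patient: the ratio per enrolled patient is (0.85·k₁)/(0.63·k₀). With k₁ = k₀ it is 1.35. If sessions rise from 2 to 4 (assumed), it is (0.85 × 4)/(0.63 × 2) = 2.70. Per session it is 1.00 in both cases. Daily sessions push k up and a shorter stay pulls it down, so 1.35 is a floor only if sessions per treated patient do not fall.

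**New-insulin row.** The text allows three readings:

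- Diabetics given steroids, as both numerator and denominator: ratio 1.00.
- Events in steroid-treated diabetics over all known diabetics: 0.70/0.43 = 1.63.
- All events in diabetics over all known diabetics, with assumed risks of 20% on and 5% off steroid: usual care 0.43 × 20% + 0.57 × 5% = 11.45%; service 0.70 × 20% + 0.30 × 5% = 15.5%; ratio 1.35. With 10% and 2%: 5.44% and 7.6%, ratio 1.40.

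Extra harm therefore cancels on one reading and stays visible on the other two.

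The fault common to all three is the events outside known diabetes. With prevalence d, mean risk m in diabetics and n in others, their share of all events is (1−d)n / [(1−d)n + dm]. The assumptions are d from 15% to 35%, the diabetic risks above, and a risk in others of 3% to 6% on steroid and 0 to 1% off.

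- Low end (d = 0.35, usual care): n = 0.43 × 3% = 1.29% and m = 11.45%. Share = 0.0084/(0.0084 + 0.0401) = 17%.
- High end (d = 0.15, service): n = 0.70 × 6% + 0.30 × 1% = 4.5% and m = 7.6%. Share = 0.0383/(0.0383 + 0.0114) = 77%.

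**The case against.** The strongest reply is that the article already contains most of what is needed. It lists hyperglycaemia as a plain incidence, collects adverse events for all enrolled patients and analyses secondary outcomes as randomised. Table 2 is a reporting table, and nothing says that its percentages are the between-condition comparison. The proportion given each treatment is reported by group, so a reader could convert the steroid row. Rates per session are also a natural safety measure for events within a session.

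Part of this stands. It shows that the remedy is cheap and that the present percentages deserve to stay. It does not remove the conflict: Table 2 is the only place that fixes a denominator for these harms, and for these five rows it departs from the outcome list and the analysis section. Multiplying a percentage by an uptake figure gives a crude rate. In a stepped wedge a crude rate mixes the intervention with calendar time. The listed reports do not include sessions per patient, so the physiotherapy rows cannot be converted in that way.

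A reader might infer more than the documents support, on three points.

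- *That all harms are masked.* They are not. Fourteen of the 19 rows, including death, fall with fracture, cardiac events, stroke, thromboembolism and gastrointestinal bleeding, carry no exposure denominator.
- *That the known-diabetic denominator cancels the effect.* Known diabetes is a baseline characteristic recorded at enrolment, not an exposure that the service raises. Cancellation needs the first reading above, which the group heading suggests but the text does not fix.
- *That control periods have no matching surveillance.* Data monitoring does say "Patients receiving routine corticosteroids as a component of the community-acquired pneumonia service interventions will be reviewed daily". But the daily data collection section covers adverse events for all enrolled patients and has glucose readings reviewed daily without limiting this to intervention periods. Whether such review fits the Blinding statement that outcomes are collected "by staff not involved in delivery of the intervention, who will be unaware of participant group allocation" is a separate question of ascertainment and does not bear on the denominators.

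**Conclusion.** The point holds for five rows of Table 2, on two distinct grounds.

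Four rows (steroid drug reaction, and falls, deterioration and ceased mobilisation in physiotherapy) cannot show extra harm that comes from wider use, and they do not compare the conditions as randomised. At constant risk per exposure they give 1.00, where the ratio per enrolled patient would be about 1.63 for steroids and 1.35 or more for physiotherapy. These sizes are illustrations and not forecasts. The 43% is any corticosteroid at audit, while the 70% is a delivery target with adherence defined by dose, timing and duration. The 63% is any physiotherapy, while the 85% is early mobilisation. The mechanism itself needs only that exposure rises, which is the purpose of the service.

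The new-insulin row omits or misplaces events in patients without known diabetes and disagrees with the plain incidence in the outcome list. The share affected cannot be known from the article. Under the assumptions shown it runs from 17% to 77%.

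**What to change.** For these five rows, define the between-condition comparison as the number of patients with at least one event over all enrolled patients under the allocated condition. Use the mixed model of Statistical methods where event counts allow, and otherwise report counts and percentages by condition. Counts may be small. The design has 8 × 5 = 40 unit-periods, 20 in each condition, so an even spread of 640 patients puts 320 in each. At an assumed 5% per recipient that gives 320 × 0.43 × 0.05 = 6.9 and 320 × 0.70 × 0.05 = 11.2 steroid reactions.

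Keep the rates per recipient and per session as labelled descriptive extras. Report new insulin for all enrolled patients and by baseline diabetes status, and state whether the row is meant to be limited to patients given steroids.

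The cost is a change of wording in Table 2 and the analysis plan, plus a few extra analyses. No new data are needed, because adverse events are already collected for all enrolled patients, and diabetes and insulin use are recorded at enrolment.
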